### Data Management and Security

Raw EMA and app engagement data do not contain Protected Health Information and will be temporarily stored in an encrypted form, with a unique study ID, in the ADAPTS app on the smartphone. When connected to the internet, encrypted data will be transferred continuously to CHOP’s secure Enterprise Amazon Web Services S3 data repository, which supports data redundancy; local EMA data on the smartphone will be deleted after successful transfer. Data will be backed up each night to a separate S3 data repository. If a participant does not connect to the internet, then the data will be temporarily stored on their smartphone. The research team also developed a password-protected study monitoring website on the CHOP network. The study monitoring website is a tool for quickly reviewing each participant’s EMA completion rates (depicts survey completion at the daily and aggregate levels) and money earned across EMA days. It is also where the RA can turn surveys on or off.

### Primary Outcome

The primary outcome is daily 6-MP adherence, measured using a validated electronic medication bottle called MEMS TrackCap. MEMS TrackCaps have two parts: (1) a standard plastic vial that stores pills and (2) a lid that contains a sensor that registers times when the vial lid is opened and closed. This method of electronic adherence monitoring has been validated in pediatric cancer, has shown consistent accuracy in independent testing, and was the same measure used in the Children’s Oncology Group study that established a 95% critical adherence level needed for relapse prevention [1,56,57]. The accompanying medAmigo software (AARDEX Group) displays the timestamped adherence data for each day. Participants will be instructed to place 6-MP in the MEMS within 24 hours of enrollment, use the MEMS each day for the full duration of the 6-month study (rather than a pillbox or pharmacy bottle), and only open the bottle if they are taking 6-MP or refilling the bottle at that time. For each day, 6-MP adherence will be classified as 1 (took dose) or 0 (missed dose).

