### Objectives

In this study, we adopted and refined an open-source EMA app called SARA [38] for an AYA cancer population (renamed ADAPTS [Adherence Assessments and Personalized Timely Support]). Through using this app, our primary study aim is to determine the temporal associations between daily contextual factors and 6-MP adherence. We draw on the pediatric self-management model [39], a social-ecological theoretical framework of disease self-management and treatment adherence, focusing primarily on the individual-and family-level contexts that could affect day-to-day medication adherence. Specifically, we hypothesize that daily fluctuations in intrapersonal (eg, physical symptoms, negative mood, and low motivation) and interpersonal or environmental (eg, a dyadic AYA-caregiver disagreement and being outside of the home without caregivers) factors will increase the odds of missing 6-MP that day. In a secondary exploratory aim, we will explore the proximal impacts of theory-informed engagement strategies (reciprocity and nonmonetary reinforcements) on daily EMA survey completion. Our approach is consistent with the first step of the Behavior Change Theories, User-Centered Design, and Social Marketing framework, a comprehensive model for creating mHealth tools, which recommends conducting a situational analysis of the contextual factors associated with a health problem [40], as well as the preparation phase of the multiphase optimization strategy [41] comprised of gathering initial information to decide which set of (engagement) components to include before an optimization trial. These formative data will ultimately inform the creation of the first JITAI for improving AYA oral chemotherapy adherence while running a concurrent JITAI for promoting EMA engagement. Improving the precision of adherence-promotion interventions in this manner may significantly benefit AYAs who require frequent self-administration of medications, as static interventions have yielded small and heterogeneous effects [42,43].

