## Methods

### Study Design

This study uses an intensive longitudinal burst design to periodically deliver EMA surveys over 6 months of maintenance chemotherapy that includes daily prescribed oral 6-MP to AYAs with acute lymphoblastic leukemia or lymphoma and their caregivers. Within the observational EMA study is an embedded microrandomized trial—an experimental design for optimizing mHealth interventions [29]—that randomizes engagement components within person and across EMAs as an early check on their efficacy before incorporating and piloting in a later JITAI.

At baseline, the enrolled AYAs and their caregivers will complete a demographic survey; brief screening measure of executive functioning; and assessment of COVID-19 exposure, impact, and distress [44] via REDCap (Research Electronic Data Capture; Vanderbilt University). Using the ADAPTS app, each participant will then receive EMA in *bursts* over the course of 6 months of maintenance therapy, capturing a time frame known to be associated with AYA 6-MP nonadherence and cancer relapse. In month 1 (28 days; ie, burst 1), EMA surveys will be sent once per day via the app to fully capture contextual processes during the month between follow-up medical appointments. To balance participant burden while also ensuring data are representative, in months 2-6, EMA surveys will be delivered once per day at the same time (6 PM), for one full week (2 weeks after the last maintenance appointment to approximate the midpoint between clinic visits when the AYA may have decreased adherence; for 35 days total), resulting in *bursts* of EMA data collection [45]. Burst designs such as this have been used to study other AYA health behaviors over a longer period [46]. Each AYA will receive a MEMS TrackCap (AARDEX Group), a validated electronic adherence monitor that was also used in the Children’s Oncology Group study, to measure daily 6-MP adherence across the entire study period.

EMA surveys are brief (<1 minute to complete) and assess intrapersonal contexts (eg, individual-level variables, such as nausea, fatigue, and positive or negative affect) and interpersonal contexts (eg, family and social environment variables, such as recent family interaction and location). Enrolled AYAs will complete 11 daily survey questions, and their caregivers will complete four survey questions (see Table 1 for a complete list of survey items).

**Table 1 table1:** Ecological momentary assessment (EMA) survey questions.

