### Human Support and Monitoring

In addition to automated engagement strategies integrated within the app, there are a few prompts that are manually sent by a member of our study team. First, after completing the first week of EMA, a standardized SMS text message will be sent to each AYA or caregiver participant to inquire about app glitches and provide a reminder to use the electronic pill bottle. Second, when a participant does not answer surveys for 3 consecutive days, they will receive an additional standardized SMS text message offering in-the-moment support for any app glitches for a maximum of one time during each EMA burst. Third, each month, a research assistant will meet briefly with families during monthly clinic visits to remind them of the study, ensure that the family is refilling MEMS bottles with 6-MP, confirm that AYAs and caregivers still have access to ADAPTS, provide financial compensation for their participation in the prior month, and download adherence data from the prior month as well as share with the AYA’s primary oncology provider. This level of human support is similar to our other prior mHealth trials [31], including the SARA trial.

To monitor for technical glitches, study staff will pull survey and engagement data each day to review whether (1) participants completed the survey from the prior day, (2) the money earned corresponds with the intended payment schedule, (3) the push notifications were sent and at the right times, and (4) participants are using the most up-to-date version of the app. Study staff will also review the list of active study participants and manually turn surveys *on* and *off* depending on their EMA burst cycle. Any technical issues will be documented in a log and shared with a technology support team within 24 hours.

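### Because adherence is coded from lid openings alone, a dose taken from another container counts as missed; if that happens more often away from home, it biases the location association in the hypothesised direction, and no planned check would show it

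*Protocol article*

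**What the plan says.** The Primary Outcome section of the protocol article describes the monitor as having "a lid that contains a sensor that registers times when the vial lid is opened and closed". Participants are told to "use the MEMS each day for the full duration of the 6-month study (rather than a pillbox or pharmacy bottle") and to open the bottle only to take or refill 6-MP. The coding rule is "For each day, 6-MP adherence will be classified as 1 (took dose) or 0 (missed dose"). It names no third state.

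Objectives lists among the contextual hypotheses "a dyadic AYA-caregiver disagreement and being outside of the home without caregivers", each expected to raise the odds of a missed dose on the same day.

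Study Design states "Enrolled AYAs will complete 11 daily survey questions"; it sets four for caregivers and presents Table 1 as the full list. Human Support and Monitoring adds a text after the first week that includes a reminder about the bottle, and a monthly meeting at which the research assistant is to "ensure that the family is refilling MEMS bottles with 6-MP" and download the month's data, which are shared with the primary oncology provider.

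Primary Data Analyses plans mixed models with a random intercept and a split into between-person and within-person predictors. It offers sensitivity analyses if data are suspected to be missing not at random. Significant findings are to inform tailoring variables for the later adaptive intervention. Limitations and Anticipated Challenges does not mention non-use of the bottle.

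**The concern.** A bottle that stays closed has two explanations: no dose was taken, or a dose was taken from somewhere else. The two-state rule leaves the second no place but 0. Random error of this kind would mostly blur the results. Here it may not be random, because a day out is a plausible occasion for carrying a pill without the bottle, and a day out without a caregiver is itself a hypothesised predictor. The exposure could then produce the recorded outcome.

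The planned model does not protect against this. The random intercept and person-mean centring remove stable differences between patients, but not non-use that varies with where the patient is that day. The missing-data sensitivity analysis does not apply, because a day coded 0 is not missing. At stake is whether location and company are taken forward as a tailoring variable on the strength of a device artefact.

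**Working it through.** **1. Is there a hidden dose item?** From Table 1, the patient items are 3 symptoms + 2 affect + 1 motivation + 3 family or social + 2 location or company = 11. The caregiver items are 2 + 2 = 4. Both totals match Study Design. The only item naming 6-MP asks about motivation. No item asks whether a dose was taken or from what container.

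**2. Inputs.**
- From the protocol article: 30 patients × 63 days = 1890 patient-days at most; about 20% nonadherence; two-sided 0.05; within-subject correlation 0.5.
- Assumed, because the documents give none: the share of taken doses that bypass the bottle on away days (qa) and home days (qh), the share of exposed days, survey completion, and how often location at the survey matches location at dosing.

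**3. Closed form with no true location effect.** With 80% of doses truly taken, the observed miss rate is 0.20 + 0.80q.
- qa 5%, qh 0%: 0.240 against 0.200. OR = (0.240/0.760)/(0.200/0.800) = 1.26.
- qa 5%, qh 2%: 0.240 against 0.216. OR = (0.240/0.760)/(0.216/0.784) = 1.15.
- qa 10%, qh 2%: 0.280 against 0.216. OR = (0.280/0.720)/(0.216/0.784) = 1.41.
- qa = qh: OR = 1.00.

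If only half of the exposed days are also away at dosing, the effective away rate is (qa + qh)/2. For 5%/2% that is 3.5%, giving 0.228 against 0.216 and OR 1.07. For 10%/2% it is 6%, giving 0.248 against 0.216 and OR 1.20.

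**4. Simulation with no true location effect.** 30 × 63 days, a person-specific random intercept (correlation 0.5 on the latent scale) and 20% true misses on average. The test is a person-stratified Mantel-Haenszel test at two-sided 0.05. Only rejections in the hypothesised direction are counted, so the nominal rate is 2.5%.

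| Non-use away / home | 20% of days exposed, all surveys completed, survey location = dosing location | 10% exposed, 80% completed, half of exposed days also away at dosing |
|---|---|---|
| 5% / 5% | about 3% | about 3% |
| 5% / 2% | 21% | 7% |
| 10% / 2% | 84% | 21% |
| 20% / 2% | 100% | 62% |

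In the right-hand column the median within-person OR is about 1.10 at 5%/2% and 1.28 at 10%/2%. With no home non-use at all (5%/0%), the left-hand setting gives 54%. A random-intercept logistic analysis in the left-hand setting gives 42% at 5%/0% and 77% at 10%/2% (OR 1.50), which is the same picture.

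**The case against.** The strongest reply is that a journal article need not describe how openings become daily codes; a reconciliation step may sit in the full protocol. That stands in part. The article never says in so many words that an unopened day is 0, and it does not say whether what the research assistant learns each month affects the coding. A reader might infer that it does not, but that would be an inference from silence. What remains is what the article does state: a lid-only sensor, two states for every day, and an item list described as complete.

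Second, the ban on other containers, the reminder and the refill check are controls, and should not be read as an admission that lapses are expected. That also stands. They reduce non-use, but none is stated to identify a particular day, and a refilled bottle does not show that every dose came from it. The cited validation of the monitor concerns its accuracy, not non-use that differs by location.

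Third, the bias is diluted. Location is asked just before a survey that opens at 6 PM, no dosing time is given, and the hypothesis combines two items (place and company). This stands, and it is why the result is given as a range.

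Two stronger readings are tempting. One is that device non-use alone would almost certainly confirm the hypothesis. That needs high non-use away, low non-use at home and a close match between survey and dosing location, none of which the documents support. The other is that a fully adherent patient would be reported to the provider as below the 95% level, since two doses outside the bottle in 28 days give 26/28 = 92.9%. The article says only that adherence data are shared. It mentions no missed-dose label or 95% verdict, and says the 95% level was itself established with the same measure.

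**Conclusion.** The point holds in a limited form. As written, the outcome is bottle opening, and a dose taken from another container is recorded as missed. Nothing in the item list or the stated sensitivity analysis would detect it. If non-use is more frequent away from home, the association with being out without a caregiver is biased towards the hypothesis. False confirmation is roughly 7-21% at 5% away and 2% at home, and 21-84% at 10% and 2%. If non-use is equal in both places and there is no true effect, there is no bias.

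These figures rest on assumed non-use rates, exposed-day shares, survey completion and agreement between survey and dosing location. They show that the artefact is possible at modest rates of non-use, not that it is present. The point concerns one group of predictors, not the study as a whole.

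**What to change.** - **Monthly visit (Human Support and Monitoring).** Have the research assistant ask about, and record, dates on which 6-MP was taken without the bottle.
- **Primary Data Analyses.** Keep the primary coding. Add a sensitivity analysis that recodes the recorded dates as taken. For all participants, including those who have finished, add a tipping-point analysis: over a stated range of away and home non-use rates, recode the implied share of unopened days as taken, refit the location and company models, and report where the association disappears. Do this before the result is used as a tailoring variable.
- **Limitations.** State that the outcome is bottle opening, and describe the monthly data shared with the provider in the same terms.

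The cost is a little more work at an existing visit, reliance on recall, and a less firm conclusion on location. Fifteen of the 30 planned dyads had already finished, so dated records can cover at most the other 15; the tipping-point analysis needs no new data.

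Two larger changes are not recommended. A daily dose item could itself alter behaviour and would change the survey mid-study. Dropping unopened days on self-report from the primary model would select on the outcome.

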### Secondary (Exploratory) Outcome

We will explore whether the microrandomized engagement content proximally affects EMA survey completion, classified as 1 (completed survey) or 0 (did not complete survey). For the celebrity quotes delivered at 4 PM, the proximal outcome is whether the survey is completed in the evening on the same day. For the post-EMA rewards (altruistic thank you messages and memes), the proximal outcome is whether the survey is completed on the following day.

### Primary Data Analyses

This data set will consist of 30 AYA-caregiver dyads×63 days=a maximum of 1890 daily observations. EMA predictors include data from AYAs, caregivers, or dyadic data from both reports (eg, agreement between AYAs and caregivers that they had a disagreement that day). Tables and graphs will be created to demonstrate how 6-MP adherence varies by individual (physical symptoms, mood, and motivation), family (family disagreements and problems with communication), and social-environmental factors (time of day, day of the week, month of the year, where AYAs were, and who they were with). Mixed effects models will be used through SAS PROC GLIMMIX (SAS Institute) to examine whether EMA of contextual factors predicted the binary daily 6-MP adherence outcome. Separate mixed effects models will be constructed for different predictors and include the predictor as the fixed effect and a random intercept for each participant to account for between-person variability. Mixed effects models may also include demographic and treatment covariates (eg, race, ethnicity, and time since cancer diagnosis) as fixed effects if they demonstrated a significant association with the outcome. We will decompose the between-subject and within-subject effects of EMA of contextual factors by creating two predictors from the original score: (1) the individual mean across all time points (between-subject predictor) and (2) the deviation of the daily score from the individual mean (within-subject predictor). Given the embedded engagement strategies, we expect minimal missing data, and mixed effects modeling will be able to use all available outcome data and provide valid inferences if missingness is at random. However, we will examine the amount and pattern of missing data, and if missing is suspected to be not at random, sensitivity analyses will be performed to assess the robustness of the primary analysis results. Significant findings will inform tailoring variables for future JITAIs (eg, tailor messages based on affect, motivation, and day of week).

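### Day-of-week effects need no survey, yet the stated data set of 63 survey days leaves out about 63-66% of the electronically monitored outcome days that could estimate them

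*Protocol article*

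**What the plan says.** Primary Data Analyses defines the data set as 30 dyads times 63 days, "a maximum of 1890 daily observations". The 63 days are the survey days. Study Design states, for the first burst, "In month 1 (28 days; ie, burst 1), EMA surveys will be sent once per day", and then one week in each of months 2-6, "for 35 days total". Sample Size and Power also works from 63 repeated measures, and Limitations and Anticipated Challenges calls the observation period 63 days.

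The outcome is recorded for much longer. Study Design gives each AYA an electronic cap "to measure daily 6-MP adherence across the entire study period", and Primary Outcome tells participants to "use the MEMS each day for the full duration of the 6-month study".

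Primary Data Analyses lists day of the week and month of the year among the factors to set against adherence in tables and graphs. It closes by saying that significant findings will inform later adaptive interventions, with the example "tailor messages based on affect, motivation, and day of week". The Introduction reports that missed doses were more common on weekends in the pilot, and says that the pilot findings need replication in a larger sample and over a longer period.

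**The concern.** A weekday analysis needs two things for each day: whether the dose was taken, and the date. Both exist for every monitored day, surveyed or not. The only data set that the protocol describes stops at the survey days, and no section says that monitored days outside the bursts enter any analysis. The remark in Primary Data Analyses that mixed models use all available outcome data concerns missing values within this set; it does not enlarge it.

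At stake is how well one candidate tailoring variable is estimated. The protocol admits that its power is not optimal for small to medium effects. For day of week, part of that shortage can be avoided with outcome data the study already plans to collect.

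**Working it through.** **Inputs from the protocol.** 30 AYAs; 28 survey days in month 1 and one 7-day week in each of months 2-6; daily monitoring for 6 months; about 20% nonadherence; within-subject correlation 0.5; two-sided alpha 0.05; 80% power.

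**Assumptions.** The protocol gives no day count for 6 months; I use 168 to 183. Weekend means 2 days in 7. The residual variances and the slope SD below are also assumed.

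**1. The plan's own figure.** 28 + 5 × 7 = 63 days, and 30 × 63 = 1890. It reproduces exactly.

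**2. Outcome days available for a calendar predictor.**
- 30 × 168 = 5040 and 30 × 183 = 5490 person-days.
- Share outside the stated set: 1 − 63/168 = 62.5%; 1 − 63/183 = 65.6%.
- Missed-dose days at 20%: 0.20 × 1890 = 378, against 0.20 × 5040 = 1008 to 0.20 × 5490 = 1098.
- Weekend days per AYA: 63 × 2/7 = 18, against 52 for 182 days.

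**3. Bias or precision?** The bursts are whole weeks, 4 + 5 = 9 of them, so each weekday occurs 9 times per AYA. The 63-day set is balanced over weekdays, and the loss is one of precision.

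**4. Standard error of a weekend effect, common slope.** The SE is proportional to 1/√days, so the ratio needs no variance assumption: √(63/168) = 0.612 and √(63/183) = 0.587. The SE falls by about 39-41%.

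**5. Weekend slopes that differ between AYAs.** SE = √[1/(n × v × 0.204) + τ²/30], where n is person-days, v the within-person variance of the outcome, 0.204 = (2/7)(5/7), and τ the slope SD. The second term does not shrink with more days. With v = 0.110 and τ = 0.5:
- n = 1890: √(0.0236 + 0.0083) = 0.179
- n = 5040: √(0.0088 + 0.0083) = 0.131
- n = 5460 (182 days): √(0.0082 + 0.0083) = 0.128

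The SE falls by about 27-28%. The formula gives 23-25% at v = 0.16 and 29-31% at v = 0.08.

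**6. Detectable weekend odds ratio at 80% power.** OR = exp[(1.960 + 0.842) × SE], for 63 against 182 days:

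| Assumptions | 63 days | 182 days |
|---|---|---|
| v = 0.20 × 0.80 = 0.16, common slope | 1.43 | 1.23 |
| v = 0.110, common slope | 1.54 | 1.29 |
| v = 0.16 × (1 − 0.5) = 0.08, common slope | 1.66 | 1.35 |
| v = 0.110, τ = 0.5 | 1.65 | 1.43 |

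Of the three variances, 0.16 follows from the protocol's 20% and 0.08 also applies its correlation of 0.5; 0.110 is an assumed value between them. The odds ratios move with these choices. The direction does not.

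**The case against.** The strongest reply is that 1890 sizes the right data set for the primary aim. The hypotheses in Objectives concern symptoms, mood, motivation, disagreements and being away from home, all known only on survey days, and the modelling text speaks of survey-measured contextual factors. That stands in full. A reader might infer that the primary analysis as a whole has been cut short; the text does not support this.

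Calendar factors also have a small role. They are listed for tables and graphs, and day of week returns once, as an example. No hypothesis names it, and a weekday model is implied rather than specified. This limits the weight of the point but does not remove it: tailoring on significant findings implies a test, and the replication goal includes the weekend effect. Nor is this mere detail left to a fuller document, because the article itself states the data set and its maximum.

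Pooling has a price. Surveyed days carry prompts, rewards and a question on motivation to take 6-MP, which the other days lack. That is fair, and it is why an indicator is needed.

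A reader might also infer that month is confounded with position in the clinic cycle. The first burst covers a full 28 days, whereas the later weeks are placed "to approximate the midpoint between clinic visits when the AYA may have decreased adherence". The documents do not support that inference. The listed factor is month of the year. Enrolment began in June 2020 with data collection expected to end by June 2022, so first bursts can start in different calendar months, and no comparison between study months is planned as a test.

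Finally, the extra monitoring data are not thrown away: they are downloaded monthly and shared with the oncology provider. They simply have no stated place in the analysis.

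**Conclusion.** The point holds for day of week only. The stated set omits about 63-66% of the outcome days usable for that predictor, on the assumption that 6 months means 168-183 days and before any loss of unusable monitoring days. With a common slope, the weekend standard error is about 1.63-1.70 times what the full record would give. The gain is smaller, but still material, if weekend effects differ between AYAs. The detectable odds ratios are illustrations under assumed variances, not properties of the trial. There is no weekday bias, no fault in the 63-day ceiling for survey predictors, and no finding on month. I rate this a cheap improvement.

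**What to change.** In Primary Data Analyses, state two data sets.

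1. **Survey days** (maximum 1890), unchanged, for all survey-measured predictors.
2. **All evaluable monitored days** over the 6 months, for day-of-week effects and for describing adherence by calendar month. Include an indicator for survey versus non-survey day and its interaction with weekend. Report the 63-day weekday estimate as a sensitivity analysis.

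Read the indicator as an adjustment, not as the effect of being surveyed: in months 2-6 the surveyed week always falls at the same point after the clinic visit, so the two cannot be separated.

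The change needs no new data collection and only a few lines of text and one additional model with its sensitivity run. The small downside is that days with and without prompts and rewards are pooled; the indicator and interaction show whether the weekend effect differs between them.

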**Objective:**

This protocol aims to determine the temporal associations between daily contextual factors and 6-mercaptopurine (6-MP) adherence and explore the proximal impact of various engagement strategies on ecological momentary assessment survey completion.

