### Study App (ADAPTS)

The finalized version of ADAPTS delivers EMA surveys to the AYAs and their caregivers, as well as several engagement strategies (Figure 1). The app is available for both iPhone and Android users. Surveys are available between 6 PM and midnight. If the surveys are not completed by 8 PM, participants will receive a reminder. Automated engagement strategies will include the following: (1) pre-EMA nonmonetary engagement strategies (inspirational celebrity quotes and survey reminders; Multimedia Appendix 1 for a complete list of quotes); (2) post-EMA nonmonetary rewards (funny memes, altruistic messages, and a growing virtual environment from an aquarium to an ocean, tundra, and then a rainforest; Figure 2 and Multimedia Appendices 2 and 3 for complete lists of memes and altruistic messages); and (3) post-EMA small monetary rewards (US $2 for completing surveys on every first day of a new EMA cycle, then US $1 for every 3-day streak with 100% completion of surveys).

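### The primary same-day model has no rule for ordering dose and evening survey, so an association can be partly reverse causation and does not by itself support the temporal aim

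*Protocol article*

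**What the plan says.** Under Objectives, "our primary study aim is to determine the temporal associations between daily contextual factors and 6-MP adherence". The hypothesis there is directional and same-day: adverse intrapersonal and interpersonal "factors will increase the odds of missing 6-MP that day".

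Study Design gives 6 PM as the delivery time. Study App (ADAPTS) adds that "Surveys are available between 6 PM and midnight". In Table 1, pain, fatigue, nausea and loneliness are asked as current states. Affect, location and company are asked as of just before the survey arrived, and motivation is asked about that day's 6-MP. The disagreement and communication questions look back over 24 hours.

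Under Primary Outcome, the MEMS software "displays the timestamped adherence data for each day", but the analysed outcome is binary: "For each day, 6-MP adherence will be classified as 1 (took dose) or 0 (missed dose").

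Primary Data Analyses will "examine whether EMA of contextual factors predicted the binary daily 6-MP adherence outcome". The within-person predictor is the day's score minus the person's mean. There is no lag, and no rule for days when the dose came before the survey. Time of day appears only among factors for descriptive tables and graphs. Significant findings are meant to inform the tailoring variables of later just-in-time adaptive interventions (JITAIs).

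**The concern.** A temporal aim needs the predictor to come before the outcome. Nothing in the article restricts dosing to the hours after the survey. If the bottle was opened at any time before the answers were given, the reported nausea, mood, motivation or company is measured after the outcome is settled.

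This error does not average out. A missed dose has no opening time, so every day on which the dose precedes the survey is a day with a dose taken. If having taken the dose changes the later answer in any systematic way, taken and missed days will differ on the predictor even when context has no effect on adherence.

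Exposure varies by item. The momentary symptom, affect, motivation, loneliness, location and company items are exposed. The 24-hour look-back items are less exposed, although their window can straddle the dose. Day of week cannot be reversed.

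At stake is the use of the results. A tailoring variable must signal a coming miss while there is time to act. An association produced by answers given after the dose cannot show that.

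**Working it through.** **1. Is the order fixed anywhere?** For the exploratory outcome, yes: the 4 PM quote is paired with that evening's survey, and the post-survey rewards with the next day's (Secondary (Exploratory) Outcome; Exploratory Analyses). For the primary outcome, no. Limitations and Anticipated Challenges does not raise it either.

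**2. The plan's own figure.** The effective sample size reproduces: 30 × 63 / (1 + 62 × 0.5) = 1890 / 32 = 59.06, against 59 stated. With n = 59 and 20% nonadherence, the standard logistic formula, n = (z_a + z_b)² / (p(1 − p)(ln OR)²(1 − R²)), gives a detectable odds ratio of 2.49. With an unstated R² of 0.2 it gives 2.77, close to the stated 2.8. The present point does not depend on this figure.

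**3. Size of the artefact when context has no effect.** Inputs from the document: 30 AYAs, 63 days, 20% nonadherence, within-subject correlation 0.5, two-sided 5% level. A random-intercept SD of 1.81 corresponds to that correlation on the logit scale: 1.81² / (1.81² + π²/3) = 3.28 / 6.57 = 0.50. Two inputs are assumptions, because the document does not give them: the share s of taken doses that precede the survey, and the shift d (in SD) that a dose already taken produces in the later answer.

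Approximation: taken and missed days differ in mean score by s × d, so with roughly unit variance ln OR per SD ≈ s × d. For d = 0.3:
- s = 25%: exp(0.075) = 1.08
- s = 50%: exp(0.15) = 1.16
- s = 75%: exp(0.225) = 1.25
- s = 100%: exp(0.30) = 1.35

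Simulated trials agree (true OR 1.00; two runs where two rejection rates are shown):

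| Shift d | Share s | OR per SD | Rejection at 5% |
|---|---|---|---|
| 0.3 | 0% | 1.00 | 4.5% |
| 0.1 | 25% | 1.03 | 4% |
| 0.1 | 50% | 1.06 | 7% |
| 0.2 | 25% | not recorded | 11% |
| 0.2 | 50% | not recorded | 31% |
| 0.3 | 25% | 1.08 | 19–22% |
| 0.3 | 50% | 1.16 | 55–57% |
| 0.3 | 75% | 1.25 | 88% |
| 0.3 | 100% | 1.35–1.36 | 98–99% |

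Larger shifts were also tried. At d = 0.5 the OR is 1.14, 1.28 and 1.68 for shares of 25%, 50% and 100%. At d = 1 it is 1.28, 1.61 and 2.91.

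**4. Do time-ordered analyses remove it?** In the simulations with d = 0.3, the next-day model gave OR 0.99 to 1.00 with 5% to 7% rejection at all shares. Restricting to days with no dose before the survey gave OR 1.00 with 4% to 6% rejection at shares of 25% to 75%.

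**5. Data available to each.** MEMS runs daily for the whole study, so the next-day model has up to 30 × 63 = 1890 pairs. If both days must lie in the same one of the six bursts, it has 30 × (63 − 6) = 1710. For the restricted analysis, 0.20 × 1890 = 378 days are misses and 1512 are taken. Days kept = 378 + (1 − s) × 1512:
- s = 25%: 1512
- s = 50%: 1134
- s = 75%: 756
- s = 100%: 378, all misses, so the model cannot be fitted

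**The case against.** **Dose times are unknown.** If nearly all doses follow the survey, the problem is small, and the motivation question reads as though the dose is still ahead. This stands as a limit on size. It does not supply an ordering rule.

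**The shift is assumed.** At 0.1 SD, rejection is near nominal. This stands, and the higher rejection rates must be read as conditional on the shift.

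**The plan quotes a detectable odds ratio of 2.8, far above 1.08 to 1.35.** A reader might infer that the spurious effects lie within the range that the plan says it can detect. They do not. The plan discounts 1890 days to 59 effective observations, whereas the simulated within-person model uses every day. What stands is that predictors are selected on significance, and the simulated rejection rates show that this can be misled.

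**A SAP could settle the order.** It could. But the article itself fixes the same-day hypothesis, the daily coding and the unlagged predictor, and followed as written they give the ambiguous result.

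**The study is formative.** The Discussion calls it an initial check, and tailoring variables are later developed with experts and other evidence. This stands and lowers the severity.

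A reader might also infer that doses taken just after midnight are scored as missed. The article says only that each day is classified. It gives neither a calendar-day definition nor a midnight cut-off, so that inference is not supported.

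**Conclusion.** The point holds as a limit on interpretation. The stated model estimates a concurrent association that may partly reflect answers given after the dose. It cannot by itself meet the aim to "determine the temporal associations between daily contextual factors and 6-mercaptopurine (6-MP) adherence" or justify a tailoring variable. The stronger reading, that the primary result will be reverse causation, is not supported: neither the share of doses taken before the survey nor the effect of dosing on later answers is known.

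Under no true effect, the artefact ranges from negligible (few doses before the survey, or a shift of about 0.1 SD) to an odds ratio of about 1.08 to 1.35 per SD, with rejection of about 20% to 99%, for an assumed 0.3 SD shift at shares of 25% to 100%. It concerns the momentary items, the 24-hour items less, and day of week not at all. This is something that should be fixed. It does not invalidate the study.

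**What to change.** 1. Rest the temporal inference on the day-t survey predicting the day t+1 dose, with person-mean centring and a random intercept as planned, adjusted for the day-t dose. The survey closes at midnight, so a dose in a following dosing day that starts no earlier than midnight comes after it whatever the submission time. The adjustment matters because doses on successive days may be correlated.
2. Add a landmark analysis: days with no bottle opening before the survey, with an opening after it as the outcome, where enough such days remain. Order events by MEMS timestamps and survey submission times. The article does not say that submission times are stored. If they are not, use the 6 PM delivery time and acknowledge that openings between delivery and answering stay unordered.
3. Fix the dosing-day boundary before analysis.
4. Report the share of taken doses that precede the survey, so that readers can place the same-day result in the range above.
5. Keep the same-day model, labelled as a concurrent association, and do not select tailoring variables from it alone.

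The cost is analysis wording and programming, with no new data collection for the next-day model. There are two real losses. The next-day model answers a different question from the same-day hypothesis, and states that change quickly may carry little into the next day. The landmark analysis loses days for AYAs who dose before the survey, and could be inestimable if nearly all do.
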